## APPENDIX B: JAIVAC\_1\_1\_09 LABORATORY REFERENCE RANGES

### JAIVAC-1\_1\_09 Laboratory Reference Ranges

| Sr #            | Analyte              | Age Limit |              |          |               | Sex   | Units   | Ref Lo   | Ref Hi |
|-----------------|----------------------|-----------|--------------|----------|---------------|-------|---------|----------|--------|
|                 |                      | Age Low   | Age Low unit | Age High | Age High Unit |       |         |          |        |
| Haematology     |                      |           |              |          |               |       |         |          |        |
| 1               | Haematocrit          | 13        | y            | 999      | y             | Males | %       | 40.0     | 54.0   |
| 2               | Haemoglobin          | 13        | y            | 999      | y             | Males | gm / dl | 13.5     | 18.0   |
| 3               | RBC Count            | 13        | y            | 999      | y             | Males | 10E6/ul | 4.60     | 6.20   |
| 4               | MCV                  | 13        | y            | 999      | y             | Males | fL      | 80.0     | 96.0   |
| 5               | MCH                  | 13        | y            | 999      | y             | Males | pg      | 27.0     | 31.0   |
| 6               | MCHC                 | 13        | y            | 999      | y             | Males | gm%     | 32.0     | 36.0   |
| 7               | WBC count            | 13        | y            | 999      | y             | Males | 10E3/ul | 4.50     | 11.00  |
| 8               | % Neutrophils        | 13        | y            | 999      | y             | Males | %       | 40.0     | 75.0   |
| 9               | % Basophils          | 13        | y            | 999      | y             | Males | %       | 0.0      | 1.0    |
| 10              | % Lymphocytes        | 13        | y            | 999      | y             | Males | %       | 20.0     | 45.0   |
| 11              | % Monocytes          | 13        | y            | 999      | y             | Males | %       | 2.0      | 10.0   |
| 12              | % Eosinophils        | 13        | y            | 999      | y             | Males | %       | 1.0      | 6.0    |
| 13              | Platelet count       | 1         | y            | 999      | y             | Males | 10E3/ul | 150      | 400    |
| Serum Chemistry |                      |           |              |          |               |       |         |          |        |
| 14              | Sodium               | 13        | y            | 999      | y             | Males | mEq / L | 136      | 145    |
| 15              | Potassium            | 13        | y            | 999      | y             | Males | mEq / L | 3.5      | 5.1    |
| 16              | Random Blood Glucose | 1         | y            | 999      | y             | Males | mg /dl  | 45       | 130    |
| 17              | Creatinine           | 16        | y            | 999      | y             | Males | mg / dl | 0.7      | 1.2    |
| 18              | Bilirubin, Total     | 1         | y            | 999      | y             | Males | mg / dl | 0.00     | 0.99   |
| 19              | Bilirubin, Indirect  | 1         | y            | 999      | y             | Males | mg / dl | 0.00     | 0.99   |
| 20              | Bilirubin, Direct    | 1         | y            | 999      | y             | Males | mg / dl | 0.00     | 0.30   |
| 21              | SGOT (AST)           | 0         | y            | 999      | y             | Males | U / L   | 0        | 40     |
| 22              | SGPT (ALT)           | 0         | y            | 999      | y             | Males | U / L   | 0        | 41     |
| 23              | γ-GT                 | 1         | y            | 999      | y             | Males | U / L   | 10       | 71     |
| 24              | Alkaline Phosphatase | 18        | y            | 999      | y             | Males | U / L   | 40       | 129    |
| Serology        |                      |           |              |          |               |       |         |          |        |
| 25              | Anti HCV             | 0         | y            | 999      | y             | Males | None    | Negative |        |
| 26              | HbsAg                | 0         | y            | 999      | y             | Males | None    | Negative |        |
| 27              | Anti-HIV             | 0         | y            | 999      | y             | Males | None    | Negative |        |

Information contained in this publication is the property of EVI and ICGEB and is confidential and will not be disclosed to third parties without written authorization from EVI and ICGEB. No part of this document may be reproduced, stored in a retrieval system or transmitted in any form or by any means -electronic, mechanical, recording or otherwise - without the prior authorization of EVI and ICGEB

[figure not shown][figure not shown]

**APPENDIX B-1: JAIVAC\_1\_1\_09 ACCEPTABLE LIMITS FOR 'OUT OF RANGE'  
LABORATORY PARAMETER(S) AT SCREENING/BASELINE**

| Sr #                   | Analyte             | Units   | Ref Lo                                                                                                    | Ref Hi |
|------------------------|---------------------|---------|-----------------------------------------------------------------------------------------------------------|--------|
| Haematology     |                     |         |                                                                                                           |        |
| 1                      | Haematocrit         | %       | If outside range as per Appendix B, then the value is to be co-related with other relevant lab parameters |        |
| 2                      | Haemoglobin         | gm / dl | 13.0                                                                                                      | 18.0   |
| 3                      | RBC Count           | 10E6/ul | 4.0                                                                                                       | 7.0    |
| 4                      | MCV                 | fL      | If outside range as per Appendix B, then the value is to be co-related with other relevant lab parameters |        |
| 5                      | MCH                 | pg      | If outside range as per Appendix B, then the value is to be co-related with other relevant lab parameters |        |
| 6                      | MCHC                | gm%     | If outside range as per Appendix B, then the value is to be co-related with other relevant lab parameters |        |
| 7                      | WBC count           | 10E3/ul | 4.0                                                                                                       | 11.0   |
| 8                      | % Neutrophils       | %       | 40.0                                                                                                      | 75.0   |
| 9                      | % Basophils         | %       | If outside range as per Appendix B, then the value is to be co-related with other relevant lab parameters |        |
| 10                     | % Lymphocytes       | %       | If outside range as per Appendix B, then the value is to be co-related with other relevant lab parameters |        |
| 11                     | % Monocytes         | %       | If outside range as per Appendix B, then the value is to be co-related with other relevant lab parameters |        |
| 12                     | % Eosinophils       | %       | 0.0                                                                                                       | 10.0   |
| 13                     | Platelet count      | 10E3/ul | 150                                                                                                       | 500    |
| Serum Chemistry |                     |         |                                                                                                           |        |
| 14                     | Creatinine          | mg / dl | 0.0                                                                                                       | 1.2    |
| 15                     | Bilirubin, Total    | mg / dl | 0.0                                                                                                       | 1.2    |
| 16                     | Bilirubin, Indirect | mg / dl | 0.0                                                                                                       | 1.2    |
| 17                     | Bilirubin, Direct   | mg / dl | 0.0                                                                                                       | 0.4    |
| 18                     | γ-GT                | U / L   | 0                                                                                                         | 71     |

*Information contained in this publication is the property of EVI and ICGEB and is confidential and will not be disclosed to third parties without written authorization from EVI and ICGEB. No part of this document may be reproduced, stored in a retrieval system or transmitted in any form or by any means -electronic, mechanical, recording or otherwise - without the prior authorization of EVI and ICGEB*

[figure not shown][figure not shown]

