## 4.2 Discussion of Overall Study Design

The present study is designed as a randomised, controlled single-blind and dose-escalating clinical study for the assessment of the safety and immunogenicity of JAIVAC-1 – Montanide ISA 720 in healthy human Indian male subjects between 18 to 45 years of age. This is a dose-escalating study and involves testing of three (3) different dosages of JAIVAC-1 malaria vaccine (PfMSP-119 and PfF2) formulated with Montanide ISA 720 as adjuvant with the intramuscular administration of the investigational vaccine as a 3-dose schedule on Days 0, 28 and 180.

30 subjects will receive JAIVAC-1 – Montanide ISA 720 (10 subjects in each cohort) and 15 subjects will receive control vaccine, Hepatitis B vaccine (5 subjects in each cohort). There will be three (3) cohorts in this study such that each cohort will consist of 15 eligible subjects randomised in a ratio of 2:1 as follows:

### Cohort 1

|                      |                                                                                                                                                                                                                                        |
|----------------------|----------------------------------------------------------------------------------------------------------------------------------------------------------------------------------------------------------------------------------------|
| Test Arm 1    | 10 subjects shall receive dosage A of investigational vaccine (0.1 ml of JAIVAC-1 vaccine containing 10µg PfMSP-1 19 and 10µg PfF2 formulated with adjuvant Montanide ISA 720) by intramuscular route on Days 0, 28 and 180 |
| Control Arm 1 | 5 subjects shall receive control vaccine (1 ml of Hepatitis B vaccine) by intramuscular route on Days 0, 28 and 180                                                                                                                    |

### Cohort 2

|                      |                                                                                                                                                                                                                                         |

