10E3/ $\mu$ L, platelet count 150 to 500  $\times$  10E3/ $\mu$ L, Neutrophils 40 to 75 % or Eosinophils > 10 %, Sodium 136 to 145 mEq/L, Potassium 3.5 to 5.1 mEq/L, Random Blood Glucose 45 to 130 mg/dl and Alkaline Phosphatase 40 to 129 U/L (Appendix B and B-1).

11. Subjects with other clinically significant abnormal laboratory values based on the normal reference range (Refer Appendix B and B1) apart from the laboratory parameters listed above.
12. Subject with positive HIV, HBV or HCV test
13. Subject with positive direct Coomb's test
14. Subject with a peripheral blood film/smear with features of haemolysis or any other haematological disorder
15. Subject unable to give written informed consent
16. Subject unable to be closely followed for social, geographic or psychological reasons
17. Subject with previous history of drug or alcohol abuse interfering with normal social function during a period of one year prior to enrolment in the study or positive urine drug test
18. Subject with an abnormal 12-lead ECG at screening associated with relevant clinical symptoms/signs suggestive of cardiac pathology (including conduction disturbances)
19. Subject with an abnormal Chest X-Ray associated with relevant clinical symptoms/signs of respiratory pathology at screening/ anytime in the past 6 months
20. Subject with known history of congenital/hereditary immunodeficiency disorders
21. Subject with acute or chronic pulmonary, reticulo-endothelial, cardiovascular, hepatic, renal or neurological condition, or any other clinical findings that in the opinion of the clinical investigator, may increase the risk of participating in the study
22. Subject with any other condition that in the opinion of the clinical investigator would jeopardise the safety or rights of a participant in the trial or would render the participant unable to comply with the protocol

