### 11.1 Study Conduct Considerations

#### 11.1.1 Sample Size

Since this is a proof of safety and immunogenicity study, true sample size calculations have not been performed and the sample size is approximately 45 healthy male subjects. Therefore no statistical hypothesis will be formulated for this study and only descriptive statistics will be provided for all parameters. The data will be described between vaccines, and within vaccines using the different strata.

A sufficient number of subjects will be screened to enrol a total number of 45 subjects in the study.

- 30 subjects will receive the investigational vaccine (i.e. JAIVAC-1 – Montanide ISA 720 malaria vaccine) with 10 subjects in each cohort and
- 15 subjects will receive the control vaccine (i.e. Hepatitis B vaccine) with five (5) subjects in each cohort.

Subjects who are discontinued from the study following enrolment and after the first (1st) vaccination (drop-outs) will not be subsequently replaced.

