#### 11.5.1.3 Analysis of Overall Safety

The safety analysis will include all randomised subjects who have received at least one dose of either of the assigned study vaccines. The overall percentage of subjects with at least one reported adverse event / serious adverse event, with date of onset up to 28 days after vaccination will be tabulated with 95% confidence intervals, by type of adverse event; by severity; and by causality. These events will be summarised and classified by System Organ Class and preferred term MedDRA. They will be displayed by vaccine group as both frequencies and percentages on the ITT data set. All reported adverse events that start post-vaccination would be tabulated. If a given disease is already reported as ongoing at the first visit on the medical history pages, it will be counted and tabulated as a vaccine emergent adverse event only if it worsens after the vaccination with the study vaccines. For each vaccine group vital sign parameters will be summarised visit wise as number of subjects, mean, SEM, median minimum, maximum and range. The changes in vital

*Information contained in this publication is the property of EVI and ICGEB and is confidential and will not be disclosed to third parties without written authorization from EVI and ICGEB. No part of this document may be reproduced, stored in a retrieval system or transmitted in any form or by any means -electronic, mechanical, recording or otherwise - without the prior authorization of EVI and ICGEB*

[figure not shown][figure not shown]

signs for every 30 minutes till 3 hours post-vaccination from pre-vaccination will be calculated and tabulated for each vaccine group.

The investigator will check the biological parameters (haematology and serum chemistry). Newly occurring or worsening lab abnormalities will be assessed and reported by the investigator as adverse events as applicable. Clinical laboratory results will be tabulated by vaccine group at each time point as both quantitative parameters (raw values) and qualitative parameters (relative positions regarding normal ranges in use in the laboratory). Serious adverse events and discontinuation due to adverse event(s) will be described in detail by vaccine group.

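### The per-visit laboratory range table cannot separate values already out of range at screening from new ones, although up to 17 of 24 analytes may be out of range at entry

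*Supplement*

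**What the plan says.** **Endpoint.** Sections 4.6.1 and 7.2.7 make laboratory safety, 28 days after each vaccination and in reference to the baseline before dose 1, part of the primary endpoint. The screening sample is that baseline, because no haematology or chemistry is drawn on Day 0 (footnotes 9 and 10 to Table 1).

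**Entry.** Exclusions 9 and 10 in section 5.4.2 and Appendix B-1 set the acceptable screening values. Several are wider than Appendix B. Exclusion 10, for example, accepts "platelet count 150 to 500" (×10³/µL), while the Appendix B platelet row reads "10E3/ul | 150 | 400". For haematocrit, MCV, MCH, MCHC, basophils, lymphocytes and monocytes, Appendix B-1 gives no number: "If outside range as per Appendix B, then the value is to be co-related with other relevant lab parameters". Exclusion 11 still bars other clinically significant abnormal values.

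**Analysis.** Section 11.5.1.3 has laboratory results "tabulated by vaccine group at each time point as both quantitative parameters (raw values) and qualitative parameters (relative positions regarding normal ranges"; the ranges meant are those of the testing laboratory. Section 11.5.1.1 plans the same kind of table among the baseline characteristics. Neither section names a cross-classification of a subject's later position by his screening position. Newly occurring or worsening abnormalities are to be reported by the investigator as adverse events, as applicable.

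**The concern.** Entry and analysis use two different sets of limits. Had entry required every value to lie inside Appendix B, any later out-of-range value would be new by construction. Because entry is wider, that holds only for the analytes whose entry limits equal Appendix B. A man admitted with platelets of 450 is high at screening and high at each later visit if nothing changes.

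The endpoint asks what changed within subjects since baseline, and a set of separate per-visit counts does not answer that. A group total can stay constant while some subjects return to range and others leave it. Such movement is plausible: eligibility and baseline rest on the same sample, section 7.1 allows no retest of abnormal screening values, and single values just outside a limit tend, as a general statistical matter, to move back towards the middle. With 10 vaccinees and 5 controls per cohort, one subject moves a percentage by 10 or 20 points.

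**Working it through.** **Step 1. Compare the limits.** Inputs are the 24 haematology and chemistry rows of Appendix B, the 18 rows of Appendix B-1, and exclusions 9 and 10 for the six analytes that Appendix B-1 omits.

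| Analyte | Appendix B | Entry limit | End widened |
|---|---|---|---|
| Haemoglobin, g/dL | 13.5–18.0 | 13.0–18.0 | low |
| WBC, 10³/µL | 4.50–11.00 | 4.0–11.0 | low |
| Creatinine, mg/dL | 0.7–1.2 | 0.0–1.2 | low |
| Gamma-GT, U/L | 10–71 | 0–71 | low |
| RBC, 10⁶/µL | 4.60–6.20 | 4.0–7.0 | both |
| Eosinophils, % | 1.0–6.0 | 0.0–10.0 | both |
| Platelets, 10³/µL | 150–400 | 150–500 | high |
| Total bilirubin, mg/dL | 0.00–0.99 | 0.0–1.2 | high |
| Indirect bilirubin, mg/dL | 0.00–0.99 | 0.0–1.2 | high |
| Direct bilirubin, mg/dL | 0.00–0.30 | 0.0–0.4 | high |

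- Wider numeric limit: 10, of which 4 at the low end only, 2 at both ends and 4 at the high end only.
- No numeric limit, subject to exclusion 11: 7 (haematocrit, MCV, MCH, MCHC, basophils, lymphocytes, monocytes).
- Same as Appendix B: 7 (neutrophils, sodium, potassium, random glucose, AST, ALT, alkaline phosphatase).

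So 10 + 7 = 17 of 24 analytes can be out of range at entry, and 24 − 17 = 7 cannot.

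**Step 2. What separate counts can show.** Let *a* be the number out of range at screening, *r* the number of those back in range at a later visit, and *k* the number newly out of range. The later count is *a* − *r* + *k*. The two tables give *a* and the later count, so they identify only *k* − *r*.

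Take one arm of 10 (section 4.2), with *a* = 2 assumed for illustration and 2 out of range at Day 28. Both tables show 2/10 (20%, exact 95% CI 2.5% to 55.6%). That is compatible with each of these:

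| Back in range, *r* | Newly out, *k* | New / in range at screening | Exact 95% CI |
|---|---|---|---|
| 0 | 0 | 0/8 (0%) | 0% to 36.9% |
| 1 | 1 | 1/8 (12.5%) | 0.3% to 52.7% |
| 2 | 2 | 2/8 (25%) | 3.2% to 65.1% |

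Intervals are Clopper-Pearson. For 0/8 the upper limit is 1 − 0.025^(1/8) = 36.9%. In a single control arm of 5, one carried-over value reads as 1/5 (20%, CI 0.5% to 71.6%) with nothing new. If the three control arms are pooled, it reads as 1/15 (6.7%, CI 0.2% to 32.0%).

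**Step 3. How often this could arise.** The documents give no frequency of out-of-range entry. If a proportion *p* of entrants is out of range on an analyte, the chance of at least one in an arm of 10 is 1 − (1 − *p*)^10. For assumed *p* of 2.5%, 5% and 10% this is 22%, 40% and 65%, for each analyte.

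**Step 4. Does adverse event reporting fill the gap?** Only in part.
- Section 8.4.2 makes an abnormal value an adverse event only if it is considered clinically significant, and under section 4.5 the investigator knows the allocation.
- The section 8.4.2 reporting window closes 28 days after each dose. The Day 180 pre-dose sample is 180 − 28 = 152 days after dose 2, and the Day 365 sample is 365 − 180 = 185 days after dose 3.
- Section 8.1 asks the investigator to look for adverse events, laboratory abnormalities included, at each visit. The visit schedule nevertheless marks no unsolicited adverse event recording at Day 365, and section 7.4.3.14 lists serious events only.
- Tables 2 to 4 grade signs and symptoms. The protocol has no numeric grading of laboratory values, so range position is its only rule-based laboratory classification.

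**The case against.** The strongest reply is that section 11 calls itself an outline and leaves full detail to a separate SAP, which is not among the documents. A shift table is ordinary SAP content, so its absence from the protocol is not an error. That stands, and it limits the weight of the point. It does not remove it. Section 11.5.1.3 does state a laboratory method, and it applies a baseline rule to its other data: a pre-existing disease counts only if it worsens, and the vital signs taken in the three hours after vaccination are tabulated as changes from pre-vaccination. Laboratory results get no such rule.

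A reader might infer that old out-of-range values will be counted as post-vaccination abnormalities and read as vaccine effects. No section says so. The endpoint refers to baseline, the baseline distribution is tabulated, and clinically significant new abnormalities have their own reporting route. What can be lost is mainly new out-of-range values not judged clinically significant.

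Nor is 17 of 24 a forecast. It counts analytes for which out-of-range entry is possible. Exclusion 11 narrows the seven without a number; creatinine and gamma-GT keep their Appendix B upper limits; and the red-cell indices and the bilirubin fractions overlap. Entry limits wider than the reference ranges are an open design choice and are not criticised here.

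Randomisation within cohort lets carried-over values fall in either arm, and no hypothesis is tested. Both are true, but neither makes the counts interpretable within subjects, and in arms of 10 and 5 chance imbalance is easy.

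**Conclusion.** The point holds in a limited form. Up to 17 of 24 analytes may be outside Appendix B at entry, and the stated per-visit table cannot distinguish values already out of range from new ones. Equal counts at two visits can mask offsetting changes. This falls short of the baseline-referenced endpoint in sections 4.6.1 and 7.2.7.

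The analyte count follows directly from the two appendices and the exclusion criteria. The size of the effect does not: it depends on how many subjects enter out of range, which is not given, and the two-in-ten example and the 22% to 65% range rest on assumptions. The documents do not support saying that safety signals will be hidden or that vaccine effects will be falsely reported. The table stated in 11.5.1.3 can be replaced by a better one at almost no cost, so this is a cheap improvement.

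**What to change.** In section 11.5.1.3, and in the SAP that carries it out:

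1. Keep range position against Appendix B, and add for each analyte and vaccine group a shift table of screening position (low, normal, high) by position at Days 28, 56, 180, 208 and 365.
2. Report the newly out-of-range subjects at each of these visits as a numerator over those in range at screening, with an exact 95% confidence interval.
3. List separately the subjects outside Appendix B at screening, with their values by visit and any change of category. Do not count such a subject as newly abnormal merely because a value lies further from the range than at screening. Without a threshold, platelets going from 450 to 451 would qualify, and that is measurement noise.

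No extra sample, visit or change to the entry limits is needed. The price is a smaller denominator wherever someone enters out of range, and so a slightly wider interval: with one such subject in an arm of 10 and no new abnormality, the upper limit is 33.6% for 0/9, against 30.8% for 0/10.
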